## Methods

### Study Design and Objectives

This study adopts a mixed methods longitudinal design to investigate the pathways through which environmental exposures influence mental health by physical activity mechanisms in Hong Kong adults.

Primary outcomes include digital biomarkers (electrodermal activity, pulse rate, and skin temperature) from wrist-worn sensors and their associations with the 3 environmental exposures of air pollution, urban density, and green-blue space access. Secondary outcomes comprise questionnaire responses, physical activity metrics from accelerometer data, and environmental exposure assessments, including mobility barriers, land use mix, road accessibility, and thermal conditions.

To address concerns regarding multiple testing, we will report the primary associations between environmental exposures and biomarkers defined above with α=.01 to minimize false positives (3 primary outcomes × 3 primary exposure measures = 9 comparisons). For secondary comparisons, we set α=.05, recognizing that this may include some false positives. However, these are exploratory analyses, and significant associations would be interpreted as suggestive to be examined with further study.

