### Digital Biomarkers Associated With Mental Health

Participants’ mental health is measured by a wrist-worn biosensor, a physiological monitoring device that captures an individual’s motion-based activity, blood volume pulse (BVP), and skin temperature and links them to physiological signals (Table 1). Skin conductance is measured in microsiemens (μS) and ranges from 2-100 μS. The sampling rate is 4 Hz. Electrodermal activity (EDA) explorer will be used to detect peaks in 5-second periods of the clean electrodermal 5-minute signal. The biosensor also assesses acceleration and rotation (actigraphy) and BVP by photoplethysmography (PPG) at sampling rates of 64 Hz, as well as peripheral (skin) temperature at sampling rates of 1 Hz.

**Table 1 table1:** Measurements for raw sensor data used in this study and their relationships with mental health.

High-frequency sensor data	Measurement method	Sampling rate	Pathway to mental health outcomes	Connection to mental health outcomes
EDA^a^	Skin conductance	4 Hz	Sympathetic nervous system activation	Higher EDA indicates increased stress and emotional arousal
BVP^b^	PPG^c^	64 Hz	Cardiovascular regulation	Irregular patterns reflect anxiety and stress states
Skin Temperature	Infrared sensor	1 Hz	Peripheral vasoconstriction	Decreased peripheral temperature indicates sympathetic nervous system activation during stress
Activity (actigraphy)	3-axis accelerometer	64 Hz	Physical activity patterns	Regular physical activity promotes positive mental health through various physiological and psychological pathways

^a^EDA: electrodermal activity.

^b^BVP: blood volume pulse.

^c^PPG: photoplethysmography.

In subsequent analysis, these raw sensor data will be processed into minute-level digital biomarkers through Empatica’s proprietary algorithms, which have been validated through prospective clinical studies sponsored by Empatica [28,29]. The digital biomarkers are aggregated into 1-minute windows, including EDA (0.01-100 μS), pulse rate (24-240 beats per minute [bpm]), skin temperature (28 °C-35 °C) as primary outcomes, as well as pulse rate variability (PRV, root-mean-square of successive difference [RMSSD] up to 300 ms), and respiratory rate (6-60 breaths per minute) as secondary outcomes. Sleep detection is also monitored, with periods categorized as awake, sleep, or interruption. All these digital biomarkers will be computed and aligned at 1-minute intervals using specific aggregation methods for each indicator.

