For secondary environmental assessments, mobility barriers will be assessed by analyzing street intersection density, obstacles, slopes, surface conditions, traffic black spots (ie, high-risk areas for accidents), and barrier-free facilities (eg, ramps, staircases, footways, lifts). These factors will be derived from government infrastructure data and 3D pedestrian network datasets within a defined radius of each GPS position. Land use mix will be quantified by the Shannon entropy index [33] from government land use raster files. Point of interest (POI) density will be computed through kernel density estimation of geocoded points from government POI databases. Road accessibility will be calculated using degree, closeness, and betweenness centrality measures will be derived from graph theory algorithms [34]. Furthermore, the thermal environment will be assessed through land surface temperature, which will be retrieved from Landsat 8 thermal infrared sensor bands using the split-window algorithm and atmospheric correction techniques.

Dynamic environmental exposure will be calculated using kernel density estimation (KDE) at multiple temporal scales based on GPS trajectories [35,36]. Specifically, we will analyze exposure at the minute level, daily level, and weekly level. This multiscale approach allows us to examine both acute and cumulative environmental exposures in relation to physical activity patterns and stress responses. It distinguishes between acute high-intensity exposures at the minute level and sustained low-intensity exposures over longer periods, which may produce equivalent cumulative values but represent distinct exposure patterns across the study period. The KDE-derived exposure surface will be integrated with environmental variables to create composite exposure metrics, which will then be temporally aligned with accelerometer-derived activity data and physiological measurements. For example, minute-level environmental exposure can be directly linked to concurrent physical activity intensity and MET values, while daily and weekly exposure metrics can be associated with aggregate activity patterns and cumulative physiological responses.

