### Data Processing and Analysis

GPS data (recorded at 1-second intervals) and physiological data from the biosensor will be temporally aligned at 1-minute intervals. To explore the relationship between environmental exposure and mental health, descriptive statistics will be computed for all variables, including biomarkers and demographic characteristics collected from biosensors and survey data. Diagnostic statistics will be applied to assess model adequacy. Outcome variables (eg, biomarkers) will be log-transformed when necessary to better approximate Gaussian distribution for residuals.

Environmental exposure will be quantified by applying kernel weights to the GPS data. This method accurately measures the precise exposure at the GPS point level, with a proximity-weighted raster surface at fine granularity (50 m × 50 m) will be constructed for the activity space of each individual [38]. For each grid cell, exposure values will be calculated based on kernel density estimation, with weights proportional to the time spent in each location.

To analyze the relationship between these environmental exposures and physiological responses, we will use multiple analytical approaches. Statistical testing will follow a hierarchical approach with α=.01 for primary analyses examining the 9 prespecified associations (3 environmental exposures × 3 digital biomarkers) and α=.05 for secondary analyses. Generalized linear mixed models will serve as our primary method to examine the direct relationships between GPS-derived exposure measures and biomarker variations, accounting for individual differences through random effects. To capture potential nonlinear relationships, we will use generalized additive mixed models. These models will be enhanced with time-series analysis techniques, including autoregressive integrated moving average models to examine temporal patterns and cross-correlation functions to identify potential lag effects between environmental exposure and physiological responses. This analytical framework allows us to understand both the immediate and delayed effects of environmental exposure on physiological responses, while accounting for individual variations and temporal dynamics.

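### Only person-level random effects are tied to the nine primary α=.01 tests on minute data; unless serial correlation enters their standard errors, the 1% error rate need not hold

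*Protocol article*

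**What the plan says.** Under Study Design and Objectives, the article counts "3 primary outcomes × 3 primary exposure measures = 9 comparisons" and sets a stricter level to limit false positives. Data Processing and Analysis repeats this as "α=.01 for primary analyses examining the 9 prespecified associations (3 environmental exposures × 3 digital biomarkers".

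The unit of analysis is the minute: "All these digital biomarkers will be computed and aligned at 1-minute intervals" (Digital Biomarkers Associated With Mental Health).

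For the primary tests, Data Processing and Analysis names generalized linear mixed models "to examine the direct relationships between GPS-derived exposure measures and biomarker variations, accounting for individual differences through random effects". Generalized additive mixed models follow for nonlinearity. Then comes: "These models will be enhanced with time-series analysis techniques, including autoregressive integrated moving average models to examine temporal patterns". The full list of time-series tools is "autoregressive integrated moving average models to examine temporal patterns and cross-correlation functions to identify potential lag effects". The paragraph closes by claiming that the framework as a whole allows both for differences between people and for change over time. Model diagnostics are promised without detail.

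Environmental Exposure Measurements adds daily and weekly exposure to the minute level and says that "daily and weekly exposure metrics can be associated with aggregate activity patterns and cumulative physiological responses". The article does not say which scale the nine tests use. The Introduction states the aim as change in exposure against change in biomarker.

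**The concern.** A person-level random intercept removes constant differences between people. It does not remove correlation between one minute and the next within a person. When exposure and residual both drift slowly, neighbouring minutes carry much less information than their number suggests, and a model that treats them as independent given the person reports standard errors that are too small.

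The design makes positive serial correlation likely in both series. Air pollution is interpolated from 18 fixed stations, exposure is kernel-weighted on a 50 m grid, and location is taken from buffers around sequential GPS points. The outcomes are one-minute summaries of EDA, pulse rate and skin temperature.

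At stake is the one error rate that the article states. The level of .01 was chosen to protect the primary claims, and it protects them only if the standard errors are right. The findings are meant to inform mental health guidelines and urban planning.

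**Working it through.** **Inputs from the article**
- α=.01 for each of nine tests. Sidedness is not stated; two-sided is assumed, so the critical value is 2.576.
- Biosensor wear of at least 18 h/day gives 5×18×60 = 5,400 to 7×18×60 = 7,560 minutes per person.
- GPS carrying of at least 1 h/day gives a minimum of 5×60 = 300 to 7×60 = 420 linked minutes per person.

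**Inputs assumed**
- Lag-1 correlations ρx (exposure) and ρe (residual within person). The article gives neither, so a range is shown.

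**Step 1: the plan's own figure.** 3×3 = 9 tests, as stated. Their levels sum to 9×.01 = .09; for independent tests the chance of at least one false positive is 1−.99⁹ = .086.

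**Step 2: effect of serial correlation.** With AR(1) exposure and AR(1) residual, the true variance of the within-person slope is V times the variance that a random-intercept-only model reports:

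V = (1+ρxρe)/(1−ρxρe), and actual rejection = 2[1−Φ(2.576/√V)].

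Example at .8/.8: ρxρe = .64, V = 1.64/.36 = 4.6, √V = 2.13, 2.576/2.13 = 1.21, rejection 22.7%.

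**Step 3: simulation under the null.** 150 people × 420 minutes, 1,000 data sets per setting, each person's minutes taken as one continuous series.

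| ρx/ρe | V | Formula | Simulated, random intercept only |
|---|---|---|---|
| 0/.9 | 1.0 | 1.0% | 1.4% |
| .5/.5 | 1.7 | 4.6% | 5.6% |
| .8/.8 | 4.6 | 22.7% | 21.6% |
| .9/.9 | 9.5 | 40.4% | 40.9% |
| .95/.95 | 19.5 | 56.0% | 54.1% |
| .98/.98 | 49.5 | 71.4% | 67.1% |

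Across the simulated settings, participant-clustered standard errors with a normal critical value gave 1.1–1.7%, and a model with AR(1) residuals gave 0.7–1.1%. The Monte Carlo standard error at a true 1% is √(.01×.99/1000) = 0.3 points.

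**Step 4: what drives it.** V depends on the product ρxρe and not on the number of minutes, so the problem is much the same at 420 minutes as at 7,560. Working backwards, 20% rejection needs V = 4.04 (product .60) and 60% needs V = 24.1 (product .92).

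**Step 5: the family of nine.** At .8/.8, if the nine tests were independent, the chance of at least one false positive would be 1−(1−.227)⁹ = .90, against .086 nominal.

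**Step 6: temporal scale.** The share of between-person information in an unsplit coefficient is λ·ICCx/(λ·ICCx+1−ICCx), with λ = σe²/(σe²+Tσu²) and T observations per person. Take an assumed outcome ICC of .5, so λ = 1/(1+T).
- Daily, T = 7, λ = .125: share .0625/.5625 = 11% at exposure ICC .5, and .1125/.2125 = 53% at .9.
- Minutes, T = 420 treated as independent, exposure ICC .9: about 2%.
- Weekly: one value per person, so 100% between-person, and a person intercept cannot be separated from residual error.

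**The case against.** The strongest reply is that the article does not leave temporal dependence out. It attaches autoregressive techniques to the mixed models and claims to allow for change over time. A reader might infer that the plan relies on random effects alone, or commits to independent residuals; the text supports neither. Random slopes and day-level terms are not ruled out. Under a random intercept, minutes are independent only given the person. A condensed article may also leave the covariance structure to an analysis plan that is not shown. All of this stands, and a missing covariance structure would not by itself be a finding.

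It does not settle the matter. The purposes stated for the time-series tools are descriptive, and a cross-correlation function cannot supply standard errors for a mixed model. Followed as written, the plan can yield primary p-values with no correction for serial correlation.

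A reader might also infer that the true error rate is a definite 20–60%. That is conditional on the model and on lag-1 products of about .60 to .92, which the documents do not give. Nor is the inflation due to thousands of minutes per person: the guaranteed GPS-linked minimum is 300 to 420, and the count hardly matters.

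Finally, one might infer that the primary tests mix within- and between-person effects through the daily and weekly metrics. Nothing in the article places those metrics among the nine tests. At the minute scale the mixing is small under the assumptions shown, and income, housing type and age are listed as covariates.

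**Conclusion.** The concern holds in conditional form. Random effects for individual differences are the only dependence handling explicitly tied to the nine primary tests, and the part played by the time-series techniques in those p-values is left open. If the tests rest on person-level random intercepts with otherwise independent minute residuals, actual rejection at nominal 1% runs from about 1% (either series uncorrelated) to 71% (.98/.98), with 23% at .8/.8. These figures rest on assumed AR(1) series and a two-sided test. The direction is clear whenever both series are positively correlated; the size is unknown until the autocorrelations are estimated. If the autoregressive structure does enter the primary error model and fits, the inflation largely disappears. The temporal scale of the nine tests and the within-person target also need to be stated, because the aim is change against change.

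**What to change.** - Report the nine primary p-values with participant-clustered robust or participant-bootstrap standard errors. Optionally add an AR(1) or continuous-time residual within participant-day.
- State that the ARIMA and cross-correlation analyses are exploratory and do not supply the primary p-values.
- State that the nine tests are at the minute level.
- Split each exposure into the person's mean and the deviation from it, and make the within-person term primary, to match the aim in the Introduction.
- Label any weekly exposure analysis as between-person and secondary.

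Clustered standard errors alone bring rejection close to 1% in the simulation; the split and the labels fix what is being estimated. Data collection is unaffected. The cost is analysis wording, some computing time and wider confidence intervals.

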### Ethical Considerations

The Human Ethics Research Committee at The University of Hong Kong approved the study procedures (award numbers: EA240125 and EA240514). Each participant provided written informed consent before the start of the experiment. Participants received an initial incentive of HKD $100 (US $12) and, upon completing the experiment, the remaining incentive of HKD $400 (US $50).

As we are collecting data with GPS locations, biomarkers, and questionnaires with personal demographic information, the sensitivity of this dataset requires high protection. The study was approved by the Human Research Ethic Committee at the University of Hong Kong. Only staff and student members listed on this ethics approval will have temporary access to study participants’ names. This information will be pseudo-anonymized for subsequent data analysis. Student helpers for data collection were all required to sign a data protection and confidentiality agreement. The data will be stored in a password-protected computer and folder managed by the corresponding author throughout the project period. Due to the large quantity of data, the corresponding author has secured access to a high-performance computing account hosted by the University of Hong Kong. All raw data will be backed up daily. All other data and codes for analytical methods can be obtained by contacting the corresponding author. The primary disseminations of our research results will comprise journal publications and presentations at academic conferences. We will also generate reports and provide evidence-based materials for policymakers to facilitate the development of more effective mental disorder intervention strategies.

## Results

This study received internal funding in May 2024 and external funding from the Health and Medical Research Fund of Hong Kong Health Bureau in July 2025. The Human Ethics Research Committee at The University of Hong Kong approved the study procedures (award numbers: EA240125 and EA240514). Each participant provides written informed consent before participating in the study.

This pilot study supported by internal funds began in September 2024. The initial setup and testing of GPS devices and biosensors were conducted from October to December 2024. As of June 30, 2025, a total of 150 participants from this pilot study had completed the 1-week experiment period, including participants from diverse population groups such as older adults and foreign domestic workers. This exploratory study aimed to validate the data collection protocol and refine study procedures, particularly focusing on device-wearing compliance and data quality assurance. As a pilot feasibility study, we monitored these feasibility metrics during data collection. We achieved a 94% (141/150) study completion rate, with participants providing ≥5 valid biosensor days and 91% (137/150) completing ≥5 of 7 daily questionnaires. These observations demonstrate the feasibility of our protocols for the larger-scale investigation.

Participant feedback sessions for protocol refinement were conducted during exit interviews throughout the pilot study period, helping identify key challenges in data collection procedures and device usage. Some participants reported difficulty with data collection during the summer months due to high temperatures and extreme weather conditions, which resulted in limited outdoor activity time and consequently reduced GPS recording coverage. A portion of participants found it challenging to maintain consistent device-wearing time, particularly during sleep or water-related activities such as swimming or showering. Several participants also noted that the limited battery life of the biosensors required frequent charging, occasionally leading to data gaps. Based on these findings, the research team has implemented enhanced support protocols with regular check-ins and reminders, detailed device management guidelines, and flexible data collection scheduling. These refinements did not change the core data collection instruments or measures, ensuring comparability between pilot and main study data.

Following the successful pilot phase, the main study, supported by the Health and Medical Research Fund, commenced in July 2025, with 30 participants enrolled and the protocol implemented as of September 2025. Full data collection for 750 participants will continue until December 2026, followed by comprehensive data analysis focusing on the associations between environmental exposure, physical activity, and mental health biomarkers. Environmental exposure data and physiological measurements are being continuously collected and processed, with specific attention to seasonal variations and weather conditions that may affect data quality. We are at an early stage of data cleaning and pre-processing for the pilot study. Data analysis is expected to be completed by June 2027, with results anticipated to be published in 2027 and 2028.

## Discussion

### Anticipated Findings

We expect to observe improved PRV and reduced EDA when exposed to green and blue spaces, with greater exposure duration and intensity associated with greater effects on these biomarkers. Conversely, we anticipate that higher air pollution levels (PM2.5, NO_2_, and AQI) and greater urban density (higher GCR and SCR) will be associated with elevated EDA and reduced PRV. This study will examine the temporal dynamics of these effects through continuous monitoring and identify the optimal duration and intensity of environmental exposures for stress reduction. We predict cumulative effects of environmental exposure on digital biomarkers associated with mental health over the study period. Participants with higher cumulative exposure to green spaces may exhibit lower baseline stress levels and better stress recovery patterns, while those with long-term exposure to air pollution and high urban density may show elevated baseline stress and impaired recovery.

Additionally, our minute-level assessment examines whether physical activity mediates the relationship between environmental exposure and stress reduction. We anticipate that physical activity, operationalized through MET, will partially mediate this relationship. Specifically, we expect moderate-to-vigorous physical activity during green-blue space exposure to strengthen the associations with lower stress levels.

Furthermore, we expect the associations between all 3 primary environmental exposure and stress biomarkers to vary across demographic subgroups and baseline mental health status. In particular, older adults and individuals with elevated baseline stress may exhibit distinct biomarker responses to environmental exposure compared to younger adults and those with lower baseline stress. As part of our secondary analyses, we will also explore associations between secondary parameters (mobility barriers, land use mix, road accessibility, and thermal environment) and additional stress-related biomarkers such as respiratory rate and sleep quality.

